### Sample Size

3.4

Because the purpose of this study was to assess feasibility rather than the effectiveness of an intervention, no formal sample size calculation was performed. However, a recruitment target of 12 participants per group was established, as previously recommended (Julious 2005).

### Data Storage and Sharing

3.5

Printed data are stored in physical files, while audio recordings and transcripts are saved digitally at the Federal University of Pernambuco. All data are retained by the principal investigator for at least 5 years.

Data sharing may occur upon a justified request to the corresponding author.

### Data Analysis

3.6

Data will be analysed using SPSS version 22.0, adopting a significance level of 5% (*p* < 0.05). All analyses will be conducted according to the intention‐to‐treat principle, with participants analysed in the groups to which they were originally randomised, regardless of adherence to the intervention protocol. As this is a feasibility study, analyses are not intended to estimate definitive treatment effects. Protocol adherence will be reported descriptively as a feasibility outcome.

Normality will be assessed using the Shapiro–Wilk test. For baseline characteristics and pre‐intervention outcomes, quantitative variables with normal distribution will be compared using the independent Student's *t*‐test. Nonparametric distributions will be analysed using the Mann–Whitney test. Categorical variables will be compared using Yates' correction, Fisher's exact test, or Pearson's chi‐square test, as appropriate.

Post‐treatment outcomes will be evaluated using analysis of covariance (ANCOVA). Each post‐intervention outcome will be modelled as a function of group (categorical factor) and its corresponding baseline value (linear covariate). Results will be expressed as mean ± standard error.

Effect size will be calculated using Cohen's d, and interpreted as follows: < 0.2 as negligible; ≥ 0.2 to ≤ 0.5 as small; ≥ 0.5 to ≤ 0.8 as moderate; and > 0.8 as large (Gignac and Szodorai 2016).

For qualitative data, the transcribed interviews will be subjected to thematic content analysis according to the Bardin framework (Bardin 2011).

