## Discussion

5

This protocol could serve as a low‐cost, easily adoptable option for physiotherapists, requiring no additional training for implementation. Its innovativeness is also significant. Although previous studies have investigated physical exercise in patients with SSc (Melchiorre et al. 2023; Parodis et al. 2023; Santos Cardozo Roque et al. 2022), most do not evaluate global disability as a primary outcome. To the authors' knowledge, no similar intervention has been proposed to date.

Potential limitations include logistical challenges related to participant attendance, a small sample size, and disease‐related complications that may influence adherence or outcomes independently of the intervention. In addition, the intervention was not developed with direct patient involvement. However, the collection of qualitative data on participants' experiences and feedback will provide valuable insights to guide future refinement of the protocol.

Uncertainty regarding the sensitivity to change of the selected outcome measures in systemic sclerosis is another limitation. Nonetheless, examining the behaviour and variability of these outcomes aligns with the objectives of a feasibility study and will inform the design of subsequent efficacy trials.

We anticipate that the study results will be published in peer‐reviewed journals, presented at regional and national conferences, and shared with participants who wish to receive this information.

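### Section 3.6 sets a 5% significance threshold, tests baseline differences, reports mean ± standard error and grades Cohen's d in words, although 12 per group cannot support those readings and the plan disclaims them

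*Protocol article*

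**What the plan says.** All the analysis choices at issue are in section 3.6 (Data Analysis) of the protocol article.

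- **Threshold:** the data are analysed "adopting a significance level of 5" per cent.
- **Disclaimer:** in the same paragraph, "analyses are not intended to estimate definitive treatment effects".
- **Baseline:** for baseline characteristics and pre-intervention outcomes, "quantitative variables with normal distribution will be compared using the independent" t-test. Mann-Whitney is used otherwise, and chi-square, Yates or Fisher for categorical variables.
- **Outcomes:** each post-intervention outcome gets its own ANCOVA on group and its own baseline value. In that paragraph, "Results will be expressed as mean" ± standard error.
- **Effect size:** Cohen's d in four verbal grades. The small band ends at 0.5 inclusive and the moderate band begins at 0.5 inclusive, so 0.5 belongs to both. No interval is mentioned.

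Section 3.4 (Sample Size) gives feasibility, not effectiveness, as the purpose. It says that "no formal sample size calculation was performed" and that "a recruitment target of 12 participants per group was established". The Discussion (section 5) adds that "examining the behaviour and variability of these outcomes aligns with the objectives of a feasibility study" and that this will inform later efficacy trials.

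**The concern.** The plan states that it will not judge efficacy, then specifies the tools used to judge it: a pass mark for p, one test per outcome, and words such as large for an effect size. In a study of 24 people, a chance p<0.05 or a large d may be quoted as a sign of benefit, and a non-significant result as a sign of failure. Neither reading would be sound.

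Two further choices add to this. If randomisation is sound, the null hypothesis of a baseline test is true by design, so its p-value tells the reader nothing useful. And a standard error describes the precision of a mean, not how much patients differ. The designer of the main trial will want that spread, and the Discussion says it is to be examined.

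**Working it through.** The article gives no effect size, SD or power, so there is no power-based figure of its own to reproduce. The stated target is 12 per group, 24 in all.

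**Inputs from the article**
- n = 12 per group (3.4); alpha = 0.05 (3.6).
- Retention of 70% is called adequate (3.1): 0.70 × 12 = 8.4, so about 8 to 9 per group.
- Outcomes with a baseline value, tallied from 3.2: SHAQ, 30-s sit-to-stand, 6-min walk, grip strength, FSS, CHFS, HADS and CD-RISC-10. That is 8, or 9 if HADS is split into two subscales. PGIC records perceived change and has no baseline value, so this ANCOVA cannot apply to it.

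**Assumptions (not in the article)**
- Two-sided tests; one score per instrument apart from HADS.
- Baseline-to-follow-up correlation r = 0.5 or 0.7; correlation between outcomes 0.3 to 0.7.

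**1. Power.** Noncentral t with noncentrality d/√(1 − r²) × √(n/2), on 2n − 2 degrees of freedom unadjusted and 2n − 3 for ANCOVA. For d = 0.5 and n = 12 the noncentrality is 0.5 × √6 = 1.22 unadjusted, and 1.22/0.866 = 1.41 at r = 0.5.

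| n per group | d | Unadjusted | ANCOVA r = 0.5 | ANCOVA r = 0.7 |
|---|---|---|---|---|
| 12 | 0.5 | 22% | 27% | 37% |
| 12 | 0.8 | 47% | 58% | 74% |
| 9 | 0.5 | 17% | 21% | 29% |

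**2. Chance of at least one false positive when no outcome is affected.**
- Independent outcomes: 1 − 0.95⁸ = 0.34; 1 − 0.95⁹ = 0.37.
- Equally correlated outcomes, by simulation of two-sample t-tests at 12 per group (20,000 runs): 30-33% at correlation 0.3, 25-27% at 0.5 and 19-21% at 0.7. The lower figure in each pair is for 8 outcomes, the higher for 9.

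**3. Smallest observed difference that is significant.**
- Unadjusted: t(0.975; 22 df) × √(2/12) = 2.074 × 0.408 = 0.85 SD. Any significant unadjusted result would therefore be graded large (above 0.8), whatever the truth.
- ANCOVA, in raw SD units and ignoring chance baseline imbalance: 2.080 × 0.408 × √(1 − r²) = 0.74 at r = 0.5 and 0.61 at r = 0.7. The link with the large grade is thus exact only for the unadjusted comparison.

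**4. Interval around d = 0.5.** SE(d) = √(2/12 + 0.5²/48) = √0.1719 = 0.415. The 95% CI is 0.5 ± 1.96 × 0.415, or -0.31 to 1.31. It includes effects in the wrong direction and every one of the four grades.

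**5. What mean ± SE conveys.** An unadjusted SE at n = 12 is 1/√12 = 0.29 of the SD, so the SD can be recovered from it and n. If the SE is that of an ANCOVA-adjusted mean, SE × √n returns roughly the residual SD, which is √(1 − r²) of the raw SD: 0.87 at r = 0.5 and 0.71 at r = 0.7. Without r, the reader cannot get from one to the other.

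**The case against.** The strongest reply is that the plan has already guarded against misreading. It disclaims definitive effects in 3.6, denies an effectiveness purpose in 3.4, calls the clinical outcomes preliminary in the abstract, and lists the small sample as a limitation. Low power is no defect where no efficacy claim is made, and exploratory outcomes commonly carry no multiplicity control. That stands as far as intent goes. It does not explain why a threshold and verbal grades are then specified.

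It is also fair that the baseline tests steer nothing: each ANCOVA covariate is fixed in advance as the outcome's own baseline value. Their harm is limited to an uninformative column in a table.

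Some stronger readings are tempting, and the documents do not support them:

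- **That supplying variability is what the study is for.** The Introduction gives the objective as recruitment, retention, acceptability, adherence, safety, costs and adverse events. Variability appears as an aim only in the Discussion.
- **That variability is lost altogether.** An unadjusted SE with n gives the SD back. The mean ± SE sentence sits in the ANCOVA paragraph, and the article does not say how baseline or raw follow-up data will be summarised.
- **That no group contrast is planned.** The ANCOVA has a group factor and Cohen's d is to be calculated. What 3.6 does not name is an interval.
- **That the main trial will come out too small by a calculable amount.** This would need a later designer to mistake a residual SD for the raw SD and then plan an unadjusted analysis. For a trial analysed by ANCOVA, the residual SD is the quantity needed.
- **That a false-alarm rate can be put on the baseline table.** The article does not say how many baseline variables will be tested.

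**Conclusion.** The concern holds in a limited form. The threshold, the baseline tests, mean ± SE and the graded d are choices that 3.6 states, not details left to a fuller document. They sit badly with the disclaimers in 3.6 and 3.4.

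For a moderate true effect, a test would miss it roughly three times in four (power 22-27%), or somewhat less often if the baseline correlation is as high as 0.7 (37%). If nothing works, the chance of at least one significant outcome is about one in five to one in three, the upper end applying if outcomes are nearly independent. Some correlation is likely, because several measures overlap (SHAQ with CHFS, sit-to-stand with walking), so the independent figures of 34-37% are best read as a ceiling for 8-9 outcomes. These sizes rest on two-sided testing, the tally of outcomes and the assumed correlations.

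No feasibility outcome is affected. What is affected is how the clinical results will be read and what can be handed to the main trial.

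**What to change.** In section 3.6:

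1. Remove the 5% threshold for clinical outcomes and the significance tests between groups at baseline; present the baseline table descriptively.
2. Report mean and SD (or median and IQR) by group at both times, with the baseline-to-follow-up correlation for each outcome.
3. Keep the ANCOVA, and report from it the adjusted between-group difference with its 95% CI, labelled as not for efficacy inference.
4. Give any standardised effect with its 95% CI and drop the verbal grades, which also removes the overlap at 0.5.

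The cost is rewording. No extra patients, visits or data are needed, and section 4 describes screening as the next step, so there is still time. The price is that there will be no p-values to quote. The new quantities will be imprecise, and openly so: at 12 per group an unadjusted difference has a 95% CI of about ±0.85 SD, and a pooled SD (22 df) one of about 0.77 to 1.42 times its estimate.

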### Feasibility Assessment

3.1

To assess the feasibility of the study, the following data will be collected (Pearson et al. 2020):Eligibility rate: the percentage of patients registered at the outpatient clinic who were eligible for recruitment;Recruitment rate: the proportion of eligible individuals who agree to participate. The number of participants recruited per month will also be estimated;Randomisation rate: the proportion of recruited participants who were successfully randomised;Retention rate: the proportion of participants who completed all planned assessments. A rate of 70% will be considered adequate (Teresi et al. 2022);Adherence rate: the proportion of participants who completed the entire protocol;Protocol fidelity: documented by recording any unplanned adaptations, including their reasons and types;Acceptability: assessed through participants' self‐reported difficulties or discomfort related to the protocol and the study. These reports will be collected as notes during each session. Acceptability will also be explored through qualitative data from semi‐structured interviews, focusing on participants' opinions and challenges during protocol implementation.

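### Minor: Cohen's d at 12 per group is biased upward in expectation by about 3.6% (5.4 to 5.8% with 17 analysed); Hedges' g removes this at no cost

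*Protocol article*

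**What the plan says.** In the protocol article, Data Analysis (3.6) gives the effect-size rule in the sentence starting "Effect size will be calculated using Cohen", which goes on to name d. The verbal bands are "< 0.2 as negligible; ≥ 0.2 to ≤ 0.5 as small; ≥ 0.5 to ≤ 0.8 as moderate; and > 0.8 as large". Post-treatment outcomes are modelled by ANCOVA with group and the baseline value of the same outcome. The section does not say whether d uses raw or adjusted means, or which SD is the standardiser, and it mentions no small-sample correction. It also states that "analyses are not intended to estimate definitive treatment effects".

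Sample Size (3.4) reports that "no formal sample size calculation was performed" and that "a recruitment target of 12 participants per group was established", so 24 in total. Feasibility Assessment (3.1) says of retention: "A rate of 70% will be considered adequate".

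**The concern.** Cohen's d divides a mean difference by an estimated SD. The reciprocal of an estimated SD is on average too large, so the mean of d over repeated trials lies further from zero than the true standardised difference. The relative size of this bias depends only on the degrees of freedom behind the SD, and it grows as they shrink. With about 22 degrees of freedom at full recruitment, and fewer after dropout, it is large enough to see in the second decimal.

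The plan will compute d for several outcomes and attach a verbal label to each. For every outcome with a true effect the bias has the same direction in expectation, so looking across outcomes does not average it out. What is at stake is modest: effects that are on average a few percent too large, and an occasional label one band too high.

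**Working it through.** The article gives no bias figure and no power calculation, so there is no figure of its own to reproduce. The check uses its stated numbers.

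**Inputs**
- 12 per group, 24 in total (Sample Size).
- 70% retention counted as adequate (Feasibility Assessment): 0.70 × 24 = 16.8, taken as 17. Assumption: those without all assessments drop out of the outcome analysis, leaving 9 and 8.
- ANCOVA with group and one covariate (Data Analysis): residual df = N − 3. For a plain pooled SD, df = N − 2. The article does not say which SD is used, so both are shown.
- Assumption: normally distributed outcomes.

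**Formula.** The expected value of d is the true value divided by J(df), where J(df) = Γ(df/2) / [√(df/2) × Γ((df − 1)/2)]. The usual approximation is J ≈ 1 − 3/(4df − 1). For df = 22 this is 1 − 3/87 = 0.9655, which agrees with the exact value to four decimals.

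| Analysed | SD used | df | J (exact) | Mean overstatement, 1/J − 1 | Reduction on correcting, 1 − J |
|---|---|---|---|---|---|
| 12 + 12 | pooled | 22 | 0.9655 | 3.6% | 3.5% |
| 12 + 12 | ANCOVA residual | 21 | 0.9638 | 3.8% | 3.6% |
| 9 + 8 | pooled | 15 | 0.9490 | 5.4% | 5.1% |
| 9 + 8 | ANCOVA residual | 14 | 0.9453 | 5.8% | 5.5% |

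**Size against sampling error** (pooled SD). SE(d) = √[N/(n1 × n2) + d²/(2N)].
- 12 + 12, true d = 0.5: bias 0.5 × 0.0358 = 0.018; SE = √(24/144 + 0.25/48) = 0.415; ratio 0.04. The approximate 95% interval around 0.5 runs from −0.31 to 1.31.
- 12 + 12, true d = 0.8: bias 0.029, SE 0.424, ratio 0.07.
- 9 + 8, true d = 0.5: bias 0.027, SE 0.493, ratio 0.05.
- 9 + 8, true d = 0.8: bias 0.043, SE 0.505, ratio 0.085.

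**Simulation** (400,000 trials, 12 + 12, normal data, pooled SD)
- True 0.5: mean d 0.519, mean g 0.501. Root mean squared error 0.437 for d and 0.421 for g.
- True 0.8: mean d 0.829, mean g 0.800.
- The correction changed the verbal band in about 4 to 5% of trials.
- A separate run at a true effect of zero gave a mean of zero for both d and g, within simulation error.

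**Worked example at 12 + 12.** An observed d of 0.50 becomes g = 0.50 × 0.9655 = 0.483, and an observed 0.80 becomes 0.772.

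**The case against.** The strongest reply is that Cohen's d is a standard choice, that an article may leave its exact formula to the full protocol or analysis plan, and that a correction there cannot be excluded. That is fair as far as it goes. However, the article does not leave the statistic open: it names d and fixes bands for it, and Hedges' g goes by a different name. Suggesting g replaces a stated estimator and does not complain of a gap.

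The second reply is that the bias is immaterial. This largely stands. It is under a tenth of the standard error in every case shown. At 12 per group and a true d of 0.5, its square is under 0.2% of the mean squared error. The lower error of g comes almost wholly from multiplying by 0.9655 and hardly at all from removing bias. The plan also disclaims definitive effect estimates.

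Two stronger readings are tempting, and neither is supported.

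- A reader might infer that each reported d will be too large. The bias is a property of the mean only. At 12 per group and a true value of 0.5, the median of d is about 0.506 and d falls below the truth in just under half of simulated trials.
- A reader might infer that a later trial would be underpowered because of this. Sizing a trial at 80% power on the expected value of d does give about 77% (24 analysed) or 76% (17 analysed), but nobody observes an expected value. When trials are sized on each simulated d or g above 0.2 (12 per group, true value 0.5, normal approximation), mean power is only a little above 60% with either statistic, so the correction does not restore 80%; sampling error dominates. The article does not propose to size the later trial on d either. Its Discussion says that the behaviour and variability of the outcomes will inform later trials.

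**Conclusion.** The point holds as a minor, free improvement. Uncorrected d overstates the true standardised difference in expectation by 3.6 to 3.8% at the stated target of 24, and by 5.4 to 5.8% with 17 analysed. The upper range needs attrition to the 70% threshold and is not the figure for full recruitment. The bias vanishes at a zero effect and is small beside the sampling error.

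The figures assume normal outcomes and an SD independent of the mean difference. They also assume that d is computed without a correction, which is the plain reading of the article but is not stated outright. The conclusion is not that the plan is in error, and no loss of power should be claimed.

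**What to change.** In Data Analysis (3.6), replace Cohen's d by Hedges' g = d × [1 − 3/(4df − 1)]. State which SD is the standardiser and take df as its residual degrees of freedom: N − 2 for a pooled SD, N − 3 for the ANCOVA residual SD, with N the number analysed for that outcome. Apply the planned bands to g.

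The cost is one term and one formula. It needs no new data, no design change and no clinical decision. Each reported effect becomes about 3.5 to 5.5% smaller, and its mean squared error falls slightly.

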### Adverse Events

3.7

Participants will be monitored for adverse events during each session. All reported or observed events will be recorded in monitoring forms by the responsible researcher.

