**Methods:**

This feasibility study protocol is designed as a randomised controlled mixed‐methods trial. It will include individuals with SSc aged 18–65 years and with a score ≥ 1 on the Scleroderma Health Assessment Questionnaire (SHAQ). Participants will be randomly allocated to either a control group, receiving an educational booklet on the disease, or an intervention group receiving the booklet plus a 10‐week supervised functional exercise protocol (twice weekly). Feasibility outcomes include recruitment and retention rates, adherence, safety, and adverse events. Preliminary clinical outcomes will address disability level, physical function, fatigue, resilience, symptoms of anxiety and depression, and perceived change. Quantitative data will be analysed using descriptive and inferential statistics, while qualitative data will undergo thematic content analysis.

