### Study Groups

2.4

Control group (CG): Participants receive an educational booklet on SSc developed by the Brazilian Society of Rheumatology (Sociedade Brasileira de Reumatologia and Comissão de Esclerose Sistêmica 2025). For those with reading difficulties, a research member will provide a video explanation via WhatsApp. Additionally, participants are instructed not to begin any physiotherapeutic intervention or exercise practice that could affect their physical conditioning during the study. After the final assessment, participants in this group will be offered follow‐up care using the study's intervention protocol.

Functional exercise group (FEG): In addition to receiving the same booklet (or video) as the CG, participants in this group individually perform a supervised functional activity‐based exercise protocol led by a physiotherapist/researcher.

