### Intervention

2.5

The protocol was developed by experienced physiotherapists specialised in the care of patients with rheumatic diseases, with consultation from a medical specialist in SSc. It is structured based on movements commonly used in activities of daily living (Papelard et al. 2019). The intervention lasts 10 weeks, with individual sessions held twice a week at the Physiotherapy Clinic of UFPE.

Each session is divided into three phases:Mobility phase—includes range‐of‐motion exercises (diagonal trunk flexion, wrist rotation, hip and knee flexion and trunk rotation) to begin the session gently. These exercises are carried out in the same manner throughout the entire intervention period.Warm‐up phase—includes upper limb cycling for 2 minutes and lower limb cycling for 4 minutes, performed throughout the entire intervention period.Functional activity‐based exercises—include pelvic lifts, upper limb mobility, trunk diagonals, sit‐to‐stand, step‐ups and step‐downs, walking circuits, and hand strengthening and mobility exercises. These exercises are divided into movements with progressive levels of complexity and load, thus aiming to approximate the training conditions to daily life activities.

Exercise difficulty progresses over the course of the intervention. The first week focuses on introducing the movements. From the second week onward, the protocol is organised into three blocks of 3 weeks each, with exercises progressing gradually within each block.

The full protocol is available in the Supporting Information S1 of this article.

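### Adverse events have a scheduled inquiry only at exercise sessions, so controls and participants who stop attending are left to passive reporting

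*Protocol article*

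**What the plan says.** The adverse-event plan is section 3.7 of the protocol article, which has two sentences. The first sets the occasion: "Participants will be monitored for adverse events during each session". The second sets the recording rule: "All reported or observed events will be recorded in monitoring forms by the responsible researcher". The second is not limited to one arm.

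Sessions belong to the exercise arm. Section 2.5 states: "The intervention lasts 10 weeks, with individual sessions held twice a week at the Physiotherapy Clinic of UFPE". For the control arm, section 2.4 states: "Participants receive an educational booklet on SSc developed by the Brazilian Society of Rheumatology", with a video explanation for those who have difficulty reading. Controls meet the exercise programme only later: "After the final assessment, participants in this group will be offered follow‐up care using the study's intervention protocol".

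Table 1 (section 3.3) has no adverse-event row. After baseline it lists the questionnaires, the physical tests and the interview at close-out. The notes on difficulty or discomfort in section 3.1 are also taken at sessions.

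Safety is nonetheless an outcome. The abstract says: "Feasibility outcomes include recruitment and retention rates, adherence, safety, and adverse events". The Introduction repeats the safety of the intervention and the reporting of adverse events as objectives, without limiting either to what happens at sessions.

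**The concern.** A rule that ties the search for events to attendance at sessions has two consequences.

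First, the arms are observed differently. The Discussion expects disease-related "complications that may influence adherence or outcomes independently of the intervention". A concurrent control arm is the natural place to see such background events. If one arm is seen by a researcher twice a week with events in mind and the other is not asked, a table of events by arm partly reflects how often people were asked. An excess in the exercise arm could then be read as harm from exercise when it is partly an effect of observation.

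Second, the channel closes when a participant stops coming. Someone who leaves the programme because of an event is among the most informative for safety and tolerability, and has no further scheduled contact at which events are monitored. This works in the opposite direction: it makes the programme look safer than it was. It applies whether or not the arms are compared.

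The future trial is meant to build on these safety results, so both distortions would carry forward.

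**Working it through.** The article gives no safety figure, event rate or power statement, so there is no figure of its own to reproduce. The check is a count of scheduled occasions, followed by arithmetic under stated assumptions.

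**Inputs**
- Intervention length and frequency: 10 weeks, 2 sessions a week (section 2.5).
- Control contact before the final assessment: booklet or video, no sessions (section 2.4).
- Target size: 12 per group, 24 in total (section 3.4).
- Retention regarded as adequate: 70% (section 3.1).
- Background 10-week risk of a reportable event: not given. Assumed range 5% to 20%.

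**Scheduled adverse-event occasions**
- Exercise participant: 10 × 2 = 20 at full attendance.
- Exercise arm: 20 × 12 = 240 at most.
- Control participant: 0 before the final assessment, and none listed at it.

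**Participants who leave**
- 70% of 24 = 16.8, so 17 must be retained and 24 − 17 = 7 may be lost with retention still called adequate.
- This counts missed assessments in both arms together. The article sets no limit on how many exercise participants may stop sessions, so the number who leave the monitoring channel cannot be bounded from it.

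**How likely there is something to find among controls**
- Chance that at least one of 12 has an event: 1 − (1 − p)^12.
- p = 5%: 1 − 0.95^12 = 0.460.
- p = 10%: 1 − 0.90^12 = 0.718.
- p = 20%: 1 − 0.80^12 = 0.931.

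These are chances that an event occurs, not that it goes unrecorded.

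**What is recorded among controls**
- If a fraction c of affected controls volunteer their event, the expected number recorded is 12 × p × c. The article gives no basis for c, so take its full range, 0 to 1.
- p = 5%: 12 × 0.05 = 0.6 affected on average, so 0 to 0.6 recorded.
- p = 10%: 1.2 affected, so 0 to 1.2 recorded.
- p = 20%: 2.4 affected, so 0 to 2.4 recorded.

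The shortfall is therefore unknown rather than demonstrably large. It is also uninterpretable, because a low control count could mean few events or little asking.

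**What a common inquiry would give**
- Each arm would have a denominator of 12.
- With 0 of 12 affected, the exact one-sided 95% upper bound is 1 − 0.05^(1/12) = 0.221, or 22%.
- With 1 of 12, the exact two-sided 95% interval is about 0.2% to 38.5%.

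Even with equal ascertainment the data can only be descriptive.

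**The case against.** The case on the other side is substantial and limits the point in four places.

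- **A reader might infer that the control arm will have no safety data.** The article does not support that. The recording rule covers reported as well as observed events in either arm, and controls attend close-out, where Table 1 schedules an interview that section 3.3 leaves open in time and content. What is absent is a planned inquiry, not every possibility of a report.
- **A reader might infer that events between sessions will be missed.** For participants still attending, this is not shown. They return twice a week, can mention an event within days, and are noted at each session for difficulty or discomfort. The concern has force for those who stop. Even there, the intention-to-treat statement in section 3.6 covers participants regardless of adherence, and nothing says that stopping sessions cancels close-out. Such events may be under-captured; it cannot be said that they will be lost.
- **A reader might infer that a planned safety comparison is invalid.** No between-arm adverse-event comparison is stated, and section 3.6 disclaims definitive effect estimates. The article also does not say that recorded events will be attributed to exercise. The problem arises once events are tabulated by arm, which a randomised study that reports safety would ordinarily do.
- **An article condenses a fuller protocol.** The monitoring forms are not shown, and the missing Table 1 row alone would be weak evidence. But section 3.7 does not leave ascertainment open. It states the occasion, and that occasion exists in one arm only. Following the rule as written produces the imbalance.

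The first three objections stand and narrow the claim. The fourth does not remove it.

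**Conclusion.** The point holds in a limited form. The only stated occasion for adverse-event monitoring is the exercise session: up to 20 per exercise participant against 0 per control before the final assessment. Controls have passive reporting only, and exercise participants who stop attending leave the only scheduled channel. Counts by arm would not be comparable, and events connected with stopping may be under-captured, for outcomes that the article names among its objectives.

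The 20-to-0 count comes from the text at full attendance and needs no assumption. The 46% to 93% chance of at least one event among 12 controls rests on an assumed 5% to 20% risk and should not be read as a rate of missed events.

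This should be fixed, but it does not undermine the other feasibility outcomes, and no stated analysis fails because of it. The article says screening is still to begin, so the change can be made prospectively. Events in controls and in those who stop are hard to reconstruct afterwards.

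**What to change.** In section 3.7 and as a new row in Table 1, add one structured adverse-event question, identical in both arms and asked at the same time points. At minimum:

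- Ask it at the existing close-out assessment, covering the whole period since randomisation.
- Put it by phone or message to anyone who stopped sessions or misses close-out, in either arm. Messaging is already used for the control video.
- Protect the blinding of Examiners A and B. For example, use a self-completed form with neutral wording that does not mention sessions or exercise, returned sealed or completed after the blinded measurements.
- Report the answers descriptively by arm with denominators, and state that 12 against 12 does not support a formal comparison. Report events recorded at sessions separately, for the exercise arm only.

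The cost is one form, one table row and a few short contacts for 24 people, with no extra visit. Additional contacts during the 10 weeks are optional. If Examiner C makes any of the contacts, blinding of A and B is preserved, but that examiner delivers the exercise and knows the allocation, so some ascertainment bias is possible. A fixed script reduces this, and the report should say who asked.
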